## Abstract

**Background:**

Health care in the United States is in the midst of a near perfect storm: strong cost pressures, dramatic redesign efforts like patient-centered medical homes and accountable care organizations, and a broad series of payment and eligibility reforms. To date, alternative models of care intended to reduce costs and improve outcomes have shown mixed effects in the U.S., in part due to the difficulty of performing rigorous evaluation studies that control for the broader transformation while avoiding other biases, such as organizational or clinic effect on individual patient outcomes. Our objective is to test whether clinics assigned to achieve high value elements (HVEs) of practice redesign are more likely than controls to achieve improvements in patient health and satisfaction with care and reduction in costs.

**Methods/Design:**

To prepare, we interview stakeholders, align with health reform, and propose a pilot. Participants are primary care clinics engaged in reform. Study protocol requires that both arms receive monthly practice facilitation, IT-based milestone reporting, and small financial incentives based on self-determined quality improvement (QI) goals; intervention receives additional prompting to choose HVEs. Design is a cluster randomized controlled trial over 1 year with pre- and post-washout periods. Outcomes are unplanned utilization and costs, patient experience of care, quality, and team performance. Analysis is a multivariate difference-in-difference with adjustments for patient risk, intraclinic correlation, and other confounders.

**Discussion:**

The TOPMED study is a cluster randomized controlled trial focused on learning how primary care practices can transform within health reform guidelines to achieve outcomes related to the Triple Aim.

**Trial registration:**

ClinicalTrials.gov registration: NCT02106221.

**Electronic supplementary material:**

The online version of this article (doi:10.1186/s13012-015-0204-6) contains supplementary material, which is available to authorized users.

## Introduction

United States health care costs per capita are more than 50% larger than other developed countries, yet our health outcomes lag in many respects [1]. To combat this disparity, the U.S. is engaged in a number of health reform efforts. For instance, billions are being invested in accountable care organizations (ACOs)—intended to virtually integrate health systems, align incentives, and optimize care for populations—and patient-centered medical homes (PCMHs)—intended to change the incentives and impact of primary care settings to better engage patients, improve quality, and improve care coordination [2]. However, the evidence about how to reform care in a complex and fragmented system is unclear [3,4] and the outcomes of previous efforts are mixed [5–8]. Although trial design has grown increasingly sophisticated over the last 20 years, designing and analyzing trials in the midst of large health reform efforts is still challenging. Analyses have shown that intervention definitions, contemporaneous trends, sample size estimates, and unit of analysis all confuse results [4]. In this paper, we describe the protocol of a complex cluster randomized controlled trial named Transforming Outcomes for Patients through Medical Home Evaluation and reDesign or TOPMED.

TOPMED is intended to test whether primary care clinics in Oregon engaged in both PCMH- and ACO-like redesign efforts can improve outcomes. In Oregon, coordinated care organizations are ACO-like models that bundle care for Medicaid patients, creating or adapting regional entities whose goals are to reduce cost of care while meeting benchmarks in quality and patient experience of care. Their primary approach involves care coordination, increased population management systems with stratification, and combining previously disparate systems like mental health, housing, and health systems in novel ways [9]. Similarly, for PCMH, Oregon chose a state recognition process (called the patient-centered primary care home) and payment reform through efforts like the Comprehensive Primary Care (CPC) initiative, funded through the Centers for Medicare and Medicaid Services (CMS), and primary care clinics are receiving a combination of proactive care management payments and shared savings to increase population management, care coordination, quality improvement, and engaging patients and families.

Previous evidence of the effectiveness of these models is mixed. Studies at Group Health, Geisinger, and Intermountain Healthcare demonstrated success [5,6,10], but several others, including the national demonstration project (NDP), a cluster randomized trial of 36 primary care clinics, improved quality metrics but failed to affect the key outcomes of cost, utilization, and patient experience [7]. Since the definitions of PCMHs are complex, we and others have identified key concepts—what we call ‘high-value elements’—that may help lead to success. In the Care Management Plus (CMP) trial at Intermountain, which studied the use of care managers embedded in seven primary care clinics compared to a set of matched control clinics, success factors included an integrated care manager, an IT-based population management system, training in complex illness care, motivational interviewing, self-management and goal setting, and how to address issues for older adults and patients identified at higher risk. In all, 1,440 patients with complex illness needs were referred during the 2-year study period. For similar patients with multiple chronic illnesses, hospitalizations were reduced by 24%–40%, patient satisfaction was higher, and patient health status was improved for those referred to care management compared to controls. Similarly, Brown et al. identified seven characteristics that defined the effective Medicare chronic care demonstration sites: 1) care coordinators with face-to-face contact with patients; 2) strong relationships with physicians; 3) patient education; 4) managing care transitions; 5) acting as a communications hub; 6) medication management; and 7) addressing psychosocial issues [3].

A number of these concepts—care coordination, care management, population management, use of IT, focusing on complex patients—are used in PCMH and ACO-like models, but most of the elements do not directly relate to known drivers of cost reduction [11]. Thus, in pursuing health reform, clinics have many different paths to choose to achieve transformation and potentially impact these outcomes. Assistance in transformation such as learning collaboratives and practice facilitation may help but does not appear to be sufficient to consistently achieve desired outcomes [12]. We wanted to understand if we could use practice facilitation coupled with IT and incentives to drive clinics towards more effective components. However, trial design in health reform is notoriously complex, with previous reviews demonstrating multiple biases and confounders that threaten study validity and success [12]. In addition, pragmatic trial design requires a protocol that can work in the real world; that is, where clinical teams need flexibility, to maintain autonomy and decision-making as much as possible, and are not burdened with additional study requests.

In our trial design process for TOPMED, we attempted to understand how one could overcome the weaknesses and mixed outcomes of previous trials. Building upon recent efforts, TOPMED integrates lessons from model implementation and trial design into health reform efforts while revising study design to account for biases. Thus, we create a trial aligned with these efforts to understand if a more targeted approach to primary care transformation is more effective than the general approach. We use a cluster randomized control trial design because our intervention involves quality improvement efforts at the organizational level of practice sites.

### Objectives

The objective of this study is to understand whether focused versus general quality improvement efforts in a pragmatic cluster randomized trial can facilitate improvement in patients’ health and satisfaction with care while reducing costs. The trial outcomes and hypotheses are both at the cluster and patient level.

The study has two major research questions:Would a study aligned with major reform efforts with focused practice facilitation, targeted incentives, and IT-based reporting enhance quality improvement capability and likely achievement of selected health reform goals within the clinics?Would a focus on a set of predetermined ‘high-value elements’ from the many choices in health reform can improve outcomes more than general quality improvement?

## Methods/Design

The proposed trial design is a cluster randomized controlled trial with a high-value element (intervention) and a general quality improvement arm (control), where randomization is at the clinic level and matching is used to minimize baseline clinic differences between arms.

### Preparation

We took several complementary approaches to explore different trial design options in the complex health reform environment for the TOPMED trial. First, we matched the trial design to the PRECIS pragmatic trial framework and reviewed trial literature. Second, we aligned trial implementation and components with major health reform elements. Third, a series of stakeholder interviews and focus groups were held to understand the values, understandings, perceptions, and intentions in regard to the health reform efforts and the potential for the trial design to be nested within these efforts. Finally, a pilot was completed to test various elements prior to the study start.

Changes to the trial design from this initial set of tasks are outlined in Table 1. The PRECIS framework recommends health professional and patient autonomy over trial protocol inflexibility and prescription, and the trial was broadened to allow flexibility in quality improvement (QI) decision-making, meeting practices where they are in terms of capacity for change. The alignment with payers and other stakeholders demonstrated that certain principles could be agreed upon, but flexibility was needed and simplification was required for specific improvement. Patients focused on access and information gaps; subsequently, we included access-related high-value elements, and all trial elements were translated to patient-specific language.

**Table 1 Tab1:** **Preparation steps for trial design**

**Aspect**	**Results**	**Changes made**
PRECIS (pragmatic trial) review	Initial high-value elements were too focused and prescriptive	Broadened to allow flexibility and health professional judgment
Alignment with health reform via multistakeholder panel (*N* = 12)	Incentives too complex; lack of alignment with other health reform efforts; team and clinic culture will drive results	Generated alignment document; revised intervention metrics and approach to better align with initiatives; extensive team and clinic assessment
Chronic illness patient focus group (*N* = 9)	Access to the clinic and the specific services need to be improved; information gaps about what is newly available (like care coordination) was common	Look carefully for patient experience measures that examine access and information gathering; expect different experiences from patients than reported by clinics; improve education
Insurer focus group (*N* = 22)	Each insurer had their own initiative or had a separate take on the current initiative set	Aligned principles were agreed to by payers; encourage payer alignment
Pilot clinic interviews (*N* = 6)	Expectations of the clinic too vague and time-consuming	Generated a memorandum of understanding that clinics revised and implemented

### Pilot study

A 6-month pilot at a single practice site was performed to test the various interventions and refine efforts. At the pilot site, preparation and protocol elements were tested in a series of six monthly practice facilitation visits. At each visit, an aspect of the trial design was tested for feasibility, clarity, and usability. The pilot team was interviewed for the results, and results demonstrated that the expectations were too vague and time-consuming. A memorandum of agreement was drawn up with specific expectations for both the research team and the clinic team. These included a role-based specification by clinic of time expected, use of data, and communication required to participate, as well as clear roles for researchers. The protocol visits by practice facilitators were honed to focus on key drivers of quality improvement and transformation: leadership, team-based approach, QI infrastructure, setting new improvement targets, and follow-up on previous improvement targets. Reports were assessed for comprehension and revised, and use of the IT system for study participation was reduced, allowing clinics to use their own protocols and tools when they matched the function of the IT system.

### Participants

Participants are eight primary care clinics (clusters) that are deeply engaged in health reform, are willing to use a population management registry tool, are willing to receive practice facilitation and improve their performance, and use an electronic health record (EHR) system at baseline. A goal was set to recruit a diverse set of participant clinics by ownership, location (rural versus urban), and size (from 3 to 20 providers). Patients, providers, and staff of these clinics are consented separately when their specific opinions or viewpoints are elicited (via surveys or interviews), with no penalty for non-participation. Data is collected at the clinics during facilitation sessions, from the EHR through automated extraction and from patients, providers, and staff via paper and online surveys.

### Interventions

The final trial design, shown in Figure 1, is a two-arm, cluster randomized controlled trial with clustering at the clinic level and stratification by size, location, and population. We considered a factorial design and a third arm with extant patient-centered medical homes but no specific interventions (usual care), but contamination prevented a factorial design and the third arm required access to unavailable clinic data.

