### Randomization

For randomization, with a small number of clusters (8), the study requires significant work to assure baseline similarities, where possible, and analytic techniques to adjust for site-specific differences. To that end, we used a sequence allocation that was computer-generated and used matching by key characteristics to place the clustered clinics into match groups. Match criteria included organization type and location; total patient population, and the number of patients that were high risk according to a standardized risk scoring system based on comorbidities that predict hospitalization. Sequence generation was done by a random number seeded by time; matched pairs of clinics are randomly allocated by this seed to either intervention or control. For the patient experience of care surveys, patients are randomly chosen by a computer program, with oversampling of ‘high risk’ at 50% of the overall sample. The principal investigator (PI) wrote the randomization algorithm, the matching criteria, and had multiple team members approve them as fair, unbiased, and without error prior to implementation. Once the program was run, it was sent directly to the other team members without intervention by the PI.

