### Statistical methods and analysis

Descriptive analysis will compare baseline characteristics of clinics and individuals across outcomes and primary confounders (demographics, chronic illnesses, previous medical care, previous adherence to quality measures). A difference in difference calculation will compare changes in rates of outcomes for intervention versus control. Primary analysis will be a multi-level, two-stage analysis to account first for patient level and clinic level differences and then changes over time. Modeling will be done using generalized estimating equations; these can be adjusted for the level and the outcome variable specifics. The risk of selection bias by cluster is high, so to account for this, we pre-assess the population by risk of hospitalization using a standardized risk score prior to trial start. This group becomes the analytic cohort, and the size of each high-risk group is used to stratify clusters. We will generate the intracluster correlation, account for it by adjusting multivariate analysis, and perform propensity matching within the analytic cohort to assure similarity of baseline cohorts at the clinics. Overfitting will be tested using Copa’s test and model fit using Hosmer-Lemeshow, receiver operating curves, and Akaike information criterion for logistic-based models and Box-Cox test, GLM family test, Link and RESET test in addition to *R*^2^, and mean-squared error for cost-based models.

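### Clinics are allocated in matched pairs, also described as strata with differing factors, while the stated GEE analysis of eight clinics names neither the pairs nor a small-sample method

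*Protocol article*

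**What the plan says.** The Protocol article describes the restricted randomization in four places.

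- Methods/Design: "matching is used to minimize baseline clinic differences between arms".
- Interventions: "stratification by size, location, and population".
- Randomization: "Match criteria included organization type and location; total patient population, and the number of patients that were high risk", the last by a standardized risk score; then "matched pairs of clinics are randomly allocated by this seed to either intervention or control".
- Statistical methods and analysis: "the size of each high-risk group is used to stratify clusters".

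On the analysis, the same last section says: "Primary analysis will be a multi-level, two-stage analysis to account first for patient level and clinic level differences and then changes over time". It adds: "Modeling will be done using generalized estimating equations". It also mentions adjustment for the intracluster correlation, propensity matching within the analytic cohort and a list of model-fit checks. The propensity matching aims at similar baseline cohorts across clinics and is not the randomized pairing. Neither the pairs nor a correction for few clusters is named.

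The Randomization section recognises the difficulty: "with a small number of clusters (8), the study requires significant work to assure baseline similarities", together with unspecified analytic techniques for site-specific differences. The ethical approval and trial status section says that analysis of the primary outcomes has not begun.

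**The concern.** Two things do not fit together.

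First, the reader cannot tell from the article which restriction was applied. Matched pairs on four criteria, strata on three factors, and strata on the size of the high-risk group are not the same statement, and the analysis should follow whichever was used.

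Second, the standard error of the arm comparison should reflect how clinics were allocated and how few there are. If paired clinics share trends, an analysis that ignores the pairs overstates the variance. If the variance comes from an uncorrected sandwich estimator on eight clusters, it is understated. These errors run in opposite directions, and which one wins depends on how well the matching worked. At stake is whether a nominal 5% test or 95% interval for cost, hospitalization and ED visits means what it says.

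**Working it through.** **Inputs from the article.** Eight clinics, hence four pairs if all are paired (Randomization); GEE difference-in-difference (Statistical methods and analysis); intracluster correlation .02 and hospitalization rate 14% (Sample size); 10% relative reduction (Outcomes and measures).

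**Assumed, because not given.** Two-sided 5% test; within-pair correlation ρ of the clinic-level changes from 0 to .8; equal clinic sizes; normally distributed clinic-level changes. The article prints no figure for this point that could be reproduced first.

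**Step 1: the allocation statements side by side.**

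| Section | Device | Factors |
|---|---|---|
| Methods/Design | matching | none listed |
| Interventions | stratification | size, location, population |
| Randomization | matched pairs | organization type, location, total patients, high-risk count |
| Statistical methods and analysis | stratification | size of high-risk group |

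Location and population overlap. Organization type and high-risk count are absent from Interventions.

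**Step 2: direction of the error.** With unit variance between clinics, the true variance of the arm difference is 2(1−ρ)/4. An unpaired estimator targets 2/4. The unpaired SE is therefore too large by 1/√(1−ρ): 1.00, 1.12, 1.41 and 2.24 at ρ = 0, .2, .5 and .8.

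Against this, the uncorrected sandwich variance with four clinics per arm divides by 4 where the unbiased estimator divides by 3. Its SE is √(3/4) = .87 of the unpaired SE, and it is referred to 1.96 where t with 6 df is 2.45.

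**Step 3: type I error.** Each clinic's change is the sum of a pair part (variance ρ) and a clinic part (variance 1−ρ), with no treatment effect and 300,000 simulated trials per setting. The variance-component test uses the paired SE with 3 df when the estimated pair variance is positive, and the unpaired SE with 6 df otherwise.

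| ρ | Sandwich z, no pairs | Unpaired t, 6 df | Paired t, 3 df | Pair variance component |
|---|---|---|---|---|
| 0 | 14.0% | 5.0% | 5.0% | 6.9% |
| .2 | 10.8% | 3.5% | 5.0% | 6.3% |
| .5 | 6.0% | 1.7% | 5.0% | 5.5% |
| .8 | 1.7% | 0.4% | 5.0% | 5.1% |

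A pair term alone is no cure. In 200,000 simulated trials, a paired sandwich z without small-sample correction had about 19% type I error at every ρ.

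**Step 4: power, for illustration only.** With a difference of 2 between-clinic SDs, power for unpaired t, paired t and variance component is 66%, 49% and 67% at ρ = 0; 67%, 57% and 71% at .2; 70%, 75% and 82% at .5; and 73%, 98% and 98% at .8.

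The 2-SD effect is an assumption. From the article's own inputs, the cross-sectional between-clinic SD of the hospitalization rate is √(.02 × .14 × .86) = .049. The planned 10% relative reduction is .014, and .014/.049 = 0.29 SD. Two SDs would be 9.8 percentage points, a 70% relative reduction.

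**The case against.** **The article does not exclude a pair term.** This stands. A condensed article may leave model terms to a full protocol or SAP, the clinic-level stage could carry the matching variables, and the Randomization section promises techniques for site differences. A reader might infer that the analysis definitely discards the pairs; the text supports only that it names none. The point survives because the section is specific about levels, stages, GEE and diagnostics, and an analysis run as printed would follow neither the pairing nor the cluster count.

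**The scheme differences are loose wording.** This stands in large part. Matched pairs are strata of size two, the list in Randomization is open-ended, and the high-risk group size is one of its criteria. One harmonized sentence would settle it.

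**Ignoring pairs makes intervals too wide.** A reader might infer this, but it fits a t-type analysis. For the GEE that the article names, without correction, the test is anti-conservative at correlations up to about .5 and conservative only when pairing is strong.

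**A large share of the precision is lost.** The documents do not support this. The within-pair correlation of changes is not given, and a difference-in-difference already removes stable clinic differences. Nor is the benefit of matching thrown away, since its stated aim of baseline balance is met by the allocation itself.

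**A randomization test could not reach 5%.** With four pairs there are 2⁴ = 16 allocations, so the smallest two-sided p is 2/16 = .125. The arithmetic is right, but no such test is planned, so this is not a fault of the plan.

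**Conclusion.** The point holds in a limited form. The allocation is described inconsistently, and the stated primary analysis names neither the matched pairs nor a small-sample method for eight clusters. Run as written with an uncorrected sandwich variance, its type I error would be about 14%, falling to about 2%, as the within-pair correlation rises from 0 to .8. An unpaired t-test would go from about 5% to 0.4%. The direction of the error cannot be settled from the article.

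The size rests on the assumed correlations, equal clinics and normal clinic-level changes, and on reading the printed analysis as complete. An unseen SAP could already resolve it. The power figures are illustrative and say nothing about this trial's actual power.

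**What to change.** Before the primary outcomes are analysed:

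1. Reconcile Methods/Design, Interventions, Randomization, and Statistical methods and analysis to one allocation scheme and one factor list, reporting what was actually done.
2. Include the matched pair in the difference-in-difference as a pair-by-period variance component, and state the small-sample degrees of freedom.
3. Report the unpaired analysis, also with a small-sample correction, as sensitivity.

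Only analysis wording changes; no new data are needed. The downsides should be stated openly. Four pairs leave few degrees of freedom. A strict paired test has 3 df (critical value 3.18 against 2.45 with 6 df) and loses power if the within-pair correlation is low. The variance-component version avoids that loss in the illustration, at the price of a type I error of about 5% to 7%.
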